#### Interim analyses

After 100 and 150 patients have undergone surgery, an interim analysis is done. Recruitment continues during the analyses. The interim analysis examines whether the difference in the primary outcome measure is significant. If this is the case, the trial is stopped and no more patients are included. If this is not the case, the trial continues. The interim analysis is performed by Forum Östergötland and only the above information is provided to the sponsor.

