### Statistics

#### Calculation of sample size

In a previous feasibility study including 30 patients undergoing robot-assisted upper urinary tract surgery under general anaesthesia without morphine spinal or intravenous lidocaine, QoR-15 decreased from a median (IQR) preoperative value of 141 (128 – 145) to 106 (88–103) on POD 1 (means (SD) 136 (11) and 105 (22); unpublished data). We assume that variance ((SD)^2^) is 400 in both groups on POD 1. With an MCID of 8, a desired alpha value of <0.05 and a power of 80% 100 subjects are needed in each group (GPower V.3.1.9.7, Heinrich-Heine-Universität Düsseldorf, Germany). To compensate for dropouts, a total of 220 subjects will be included in the trial.

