#### Analysis groups

The primary outcome is analysed in the entire trial group according to the intention-to-treat (ITT) principle, except for the subjects who do not undergo the planned robot-assisted surgery within 12 months from inclusion, and/or neither receive intervention nor control treatment, and/or leave the trial and/or die before the POD 1 measurement. The clinical secondary analyses are also analysed in this entire trial group according to ITT. These analyses will be supplemented with:

A per protocol (PP) analysis of the primary hypothesis as well as NRS POD 1–3, where subjects who are included in the ITT analysis, however, without sufficient preoperative effect of the spinal analgesia, and/or where lidocaine infusion was prematurely terminated, and/or where the surgery was converted to an open procedure are excluded.An ITT and PP analysis as above where subjects with problematic pain are omitted. Problematic pain is defined here as preoperative opioid use for more than 1 month.

The haemodynamic and biochemical parameters are analysed only in the subgroup that is monitored with advanced haemodynamic monitoring according to the PP principle, that is, subjects with a spinal anaesthetic without adequate preoperative spread, and/or where lidocaine infusion was prematurely terminated, and/or where the surgery was converted to an open procedure are excluded.

Normal distribution will be tested with the Shapiro-Wilks test, except for QoR-15 and NRS data which are assumed to be not normally distributed. All significance tests are done two-sided. A p value lower than 0.05 is considered significant. No corrections for multiple comparisons are made unless otherwise specified.

Single missing values are in principle not imputed. In exceptional cases, if missing data cause an entire data series (in time) to be misleading, the missing data can be imputed with the average value of the two measurements closest in time, provided that this results in a reasonable value.

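### Two interim looks that stop the trial at an unadjusted p < 0.05 raise the two-sided type I error from 5% to about 10% and exaggerate the effect when the trial stops early

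*Protocol article*

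**What the plan says.** Under Interim analyses, the protocol article sets two looks: "After 100 and 150 patients have undergone surgery, an interim analysis is done". The decision rule follows: "The interim analysis examines whether the difference in the primary outcome measure is significant. If this is the case, the trial is stopped"; otherwise the trial continues. No p-value boundary, alpha-spending function or reduced final level appears there.

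The threshold comes from the general statements under Analysis groups: "All significance tests are done two-sided", and "A p value lower than 0.05 is considered significant. No corrections for multiple comparisons are made unless otherwise specified".

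Under Calculation of sample size, the trial is planned as follows: "With an MCID of 8, a desired alpha value of <0.05 and a power of 80" per cent. With a variance of 400 this gives 100 subjects per group, and 220 are included to allow for dropout. The design section describes the trial as phase III and therapeutic confirmatory.

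**The concern.** Read together, these sections give the trial three opportunities to declare success at 0.05: at 100 patients, at 150 and at the end. A difference that arises by chance at any one of them counts as a positive result, so the overall false-positive risk must exceed the 5% that the sample size section claims.

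A threshold of 0.05 at half the planned sample is also easy to cross, and it is crossed preferentially when the observed difference happens to be large. A trial that stops there tends to report too large an effect. It also leaves the safety and secondary outcomes with little more than half the planned data. The authors expect the result either to support morphine spinal in this and similar surgery or to justify omitting it, so both problems bear directly on the use of the trial.

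**Working it through.** **Inputs.** Looks after 100 and 150 patients (Interim analyses). Final analysis at 200 evaluable or 220 included patients; difference 8, variance 400 (SD 20), alpha 0.05 and power 80% (Calculation of sample size). Two-sided p < 0.05 (Analysis groups). Allocation 1:1 (Inclusion and randomisation).

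**1. The plan's own figure.** A two-sample t-test with difference 8, SD 20, two-sided alpha 0.05 and power 80% needs 100 per group (99 by the normal approximation). The stated 100 is reproduced. It is a single-look calculation with no allowance for interim testing.

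**2. Overall type I error.** Under no difference, the test statistics at total sizes N_i < N_j are approximately jointly normal with correlation √(N_i/N_j). For 100/150/200 the correlations are √(100/150) = 0.816, √(100/200) = 0.707 and √(150/200) = 0.866. The error is 1 − P(|Z| ≤ 1.96 at every look).

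| Looks | Overall two-sided type I error |
|---|---|
| 100, 150 only | 7.7% |
| 100, 150, 200 | 9.7% |
| 100, 150, 220 | 10.0% |

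For 100/150/200 the simulated contributions of the three looks are 5.0%, 2.7% and 2.0%. Simulating the planned Mann-Whitney test instead of the normal approximation gives 9.8% with a final 200 and 10.2% with 220.

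**3. Estimate on early stopping.** The standard error of the difference at 100 patients is 20 × √(4/100) = 4, so significance needs an observed difference of at least 1.96 × 4 = 7.84. With a true difference of 8 the expected Z is 8/4 = 2.

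- Chance of stopping at look 1: P(Z > 1.96) = Φ(0.04) = 0.516.
- Mean Z given such a stop: 2 + φ(0.04)/0.516 = 2 + 0.399/0.516 = 2.773.
- Mean estimate: 2.773 × 4 = 11.1 points, and 11.1/8 = 1.39, so 39% too large.

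Simulation for looks at 100/150/200:

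| True difference | P(stop at 100) | Mean estimate at 100 | Mean estimate at 150 | Mean over early stops |
|---|---|---|---|---|
| 8 | 0.52 | 11.1 | 8.06 | 10.2 |
| 6 | 0.32 | 10.4 | 7.8 | 9.5 |
| 4 | 0.17 | 9.8 | 7.5 | 8.9 |

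With a true difference of 8, the mean over all trials, stopped or not, is 8.8.

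**4. Boundaries that hold 5%, looks at 100/150/200.**

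| Rule | Nominal two-sided p at the three looks | Overall alpha | Power at 8 points |
|---|---|---|---|
| As written | 0.05 / 0.05 / 0.05 | 9.7% | 84.1% |
| Single look at 200 | – / – / 0.05 | 5.0% | 80.7% |
| Lan-DeMets O'Brien-Fleming-type, 0.025 spent per side | 0.003 / 0.018 / 0.044 | 5.0% | 80.0% |
| Lan-DeMets O'Brien-Fleming-type, total 0.05 in one spending function | 0.006 / 0.022 / 0.041 | 5.0% | 79.5% |
| Classical O'Brien-Fleming | 0.0042 / 0.0194 / 0.0430 | 5.0% | 79.8% |
| Haybittle-Peto | 0.001 / 0.001 / 0.05 | 5.02% | 80.8% |

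With a final analysis at 220, the per-side spending version becomes 0.002 / 0.013 / 0.046, with power 83.8%.

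**The case against.** The strongest reply is that the interim section gives no p-value. The 0.05 is carried over from a general paragraph whose remark on multiple comparisons may have been meant for endpoints, and a full protocol or analysis plan that is not shown could set a boundary. That possibility is real, but the article is not merely silent. It defines significance once, states "No corrections for multiple comparisons are made unless otherwise specified", and writes a stopping rule that specifies nothing different. A boundary held elsewhere would conflict with this text, which would still need correction. Having Forum Östergötland run the looks and limit what reaches the sponsor protects trial conduct; it does not control type I error.

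Several narrower points do stand:

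- The 39% applies only to stops at 100 patients. Stops at 150 are nearly unbiased if the true difference is 8, and over all trials the excess is about 10% (8.8 against 8).
- Some exaggeration after early stopping occurs under any boundary. The loose threshold makes such stops frequent.
- Recruitment continues during the interim analyses, so a stop at the first look would leave somewhat more than half the data.
- Looks are triggered by patients operated. If the final analysis has 220 patients, they fall at 45% and 68% of the information, not 50% and 75%, and the boundary changes accordingly.
- Against the rule as written, a valid boundary costs about 3 to 5 points of power (84.1% to between 79.5% and 80.8%). That comparison is with a rule that gains its power from the inflated error.

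**Conclusion.** The stopping rule is wrong as written. It gives an overall two-sided type I error of about 10% (9.7% to 10.2%, depending on the final size and on whether the normal approximation or the Mann-Whitney test is used) where the sample size section claims less than 5%. About 7.7% is already spent by the second look. If the planning assumptions are true, the trial stops at 100 patients about half the time and then reports on average 11.1 points for a true 8. Even a true difference of 4 would average 9.8 at such stops, above the chosen MCID of 8.

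The type I error figure rests on equal allocation, approximately normal test statistics and the stated numbers at each look. The bias figures also need the assumed SD of 20. All of it takes 0.05 as the interim threshold, the only one the article gives. For a confirmatory trial this must be corrected before the first look.

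**What to change.** Amend the Interim analyses section, and the full protocol or analysis plan with it, as follows.

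1. Replace the word significant with a named boundary. One choice is Lan-DeMets O'Brien-Fleming-type spending at an overall two-sided 0.05, stating whether 0.025 is spent on each side, with critical values computed from the evaluable patients at each look. At 50%, 75% and 100% information the nominal p-values are about 0.003, 0.018 and 0.044 with spending per side, or about 0.006, 0.022 and 0.041 with the total 0.05 in one function. A simpler choice is Haybittle-Peto: p < 0.001 at both looks and 0.05 at the end.
2. State the final significance level that goes with the chosen boundary, and say that it overrides the general 0.05 rule for the primary outcome.
3. If the trial stops early, report an estimate and confidence interval adjusted for the stopping rule, and include in the analysis the patients recruited while the interim was running.

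The cost is one paragraph and an amendment. At 200 patients, power against a single-look design falls by about 1 percentage point or less with O'Brien-Fleming-type spending, and not measurably with Haybittle-Peto. Early stopping becomes less likely.

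The article reports 54 patients included by 1 October 2025, so the first look had not been reached then. It was published on 6 May 2026, and how near that look now is cannot be told from the text, so the amendment should be filed promptly. If a look at 0.05 has already been taken, that error has been spent, and the remaining boundary would have to account for it.

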### Blinding

Blinding of the subject and the anaesthesiologist in charge of the patient is not performed. Group allocation is not recorded in the CRF (case record file), only a checkbox with ‘Has the patient received the planned treatment (morphine spinal or lidocaine infusion) as planned yes/no’. The spinal analgesia or lidocaine infusion is documented on the randomisation paper which is kept separately from the CRF. Spinal analgesia or lidocaine infusion is also documented in the usual way in the anaesthesia journal. This information is visible when trial data are transferred from the anaesthesia record to the CRF but not later during data analysis. When the subject is contacted postoperatively, it should not be actively sought whether the subject has received a spinal anaesthetic or not. Should this information still come to light, no note is made of this. However, if the person who collects the QoR-15 on POD 1 has, for some reason, received information about the treatment method before the QoR-15 has been recorded, this must be recorded on the PD (protocol deviation) log. Group affiliation is not noted in the diary. The randomisation code is broken only when data acquisition is completed. In case of emergency, code breaking takes place through a review of the subject’s anaesthesia record.

### Ethics

This study is performed in accordance with the Declaration of Helsinki and Good Clinical Practice. The original study protocol was approved by the Swedish Medical Products Agency on 27 October 2023 (5.1.1-2023-69740). A significant modification was approved on 12 May 2025 (5.1.2-2025-030145). The study is registered at Clinical Trials Information System (CTIS; 2023–5 05 941-21-00) and ClinicalTrials.gov (NCT06349668; date of first registration 29 March 2024). Substantial changes to the signed protocol are only possible through approved protocol changes in the CTIS and will be communicated to all participating sites.

We have shown in a feasibility study that robot-assisted upper urinary tract surgery leads to a significant reduction in early postoperative well-being. Most patients also experience severe pain. There is thus a clear need for strategies that improve well-being after robot-assisted upper urinary tract surgery. The main hypothesis of the trial is that the addition of morphine spinal in robot-assisted upper urinary tract surgery results in improved recovery.

The reduced sympathetic effect resulting from a spinal anaesthetic may result in hypotension, which may require treatment with intravenous fluids and/or vasopressors. This is standard procedure in anaesthesia and is not expected to cause any increased risk to the subjects. In some unusual conditions, such as severe aortic valve stenosis, the risks associated with a reduced sympathetic effect increase and patients with these conditions are excluded.

The risk of severe neurological complications caused by bleeding, trauma or infection in connection with the administration of spinal analgesia has been reported to be approximately 1:25 000.^41^ This should be related to the fact that the risk of death within 30 days after an operation in Sweden has been reported to be 1:50.^42^ Therefore, even a moderate positive effect of morphine spinal on the postoperative course far outweighs its risks. Patients with risk factors for complications related to spinal analgesia such as coagulopathy, previous lumbar spine surgery with osteosynthesis material, severe local or systemic infections and severe spinal deformities are excluded. The application of spinal analgesia will be aborted if it is difficult or if it causes severe discomfort for the patient.

Due to the disadvantages of morphine spinal, it is clinically relevant to investigate whether morphine spinal is actually better than an alternative additional treatment without the disadvantages of morphine spinal. Of the possible strategies considered to have the potential to approach equivalent effect on postoperative recovery as a morphine spinal, only intravenous lidocaine is not associated with renal effects or a negative effect on tumour progression.

Lidocaine given intravenously perioperatively for pain relief is a so-called ‘off-label’ use, similar to many other drugs used in anaesthesia, for example, epidural fentanyl. The use of lidocaine in this way is currently limited in Sweden, but it is routine in many hospitals abroad and is recommended in various international guidelines.^24 25^ The bolus dose and infusion rate in the current trial are well in line with previous studies on the effect of lidocaine as a pain-relieving drug given intravenously.^13^

The lidocaine infusion will be started and finished while the subject is closely monitored in the operating room. Signs of systemic toxicity will thus be detected early and treatment rapidly initiated. The relatively short treatment time means that the risk of accumulation and late toxicity is considered negligible, even in subjects with pre-existing or new-onset renal failure. The infusion is stopped prematurely if severe unexplained hypotension or arrhythmia occurs. Patients with severe kidney or liver failure or advanced heart disease will not be included in the trial. The use of larger doses of local anaesthetic in other ways during the primary operation is not permitted in those receiving lidocaine.

The trial involves the handling of sensitive personal data. The risk of various forms of privacy infringement is minimised through informed consent and pseudonymised processing and storage of research data, including sample material.

### Protocol adherence

Intervention and comparator groups will receive the treatment only on one occasion (preoperatively and intraoperatively, respectively). An anaesthetist will provide the intrathecal analgesia and anaesthesia staff will administer the intravenous lidocaine. Drug administration is routinely documented in the anaesthesia record as well as in a separate trial drug log.

Study staff will visit the subject in the surgical ward to obtain the QoR-15 on POD 1 (primary outcome). Study staff will try to reach the subject on telephone on POD 7 between 09:00 and 21:00. On that occasion, the subject will also be reminded to send in the diary if not already done. For subjects who withdraw from the study, no additional data will be collected; however, previously collected data will be analysed.

### Monitoring

The trial will be monitored by Forum Östergötland before the trial begins, during the course of the trial and after the trial has ended. The first visit at each site will take place after 1–2 subjects have completed the 30-day follow-up in the study. Thereafter, monitoring will take place each time 20 new subjects have completed the 30-day follow-up. The process will be independent of the investigators and the sponsor.

The study also is monitored by a data safety monitoring board, which consists of three individuals with relevant clinical experience. After an introductory meeting, the board and sponsor will meet after the inclusion of the 10th patient participating in the trial. Hereafter, the board will meet at least twice every year.

A safety report is submitted annually to the Swedish Medical Products Agency.

### Ancillary and post-trial care

In case of trial-related adverse events, the subject will be followed by the sponsor in addition to the attending physician until the event has ended or until the condition has become chronic. Regular patient insurance and extended pharmaceutical insurance apply.

### Data protection and storage

Trial data are stored to maintain confidentiality in accordance with national data legislation. Investigator file, consent form, CRF and key to social security number will be stored in locked rooms during the trial. After completion of the study, these data will be archived in accordance with national legislation. All data processed by the sponsor will be pseudonymised and identified by trial ID.

### Dissemination

The results of this study will be presented at national and international meetings and submitted for publication in peer-reviewed international medical journals.

### Trial status

The first patient was included on 9 April 2024. As of 1 October 2025, 54 patients have been included. A second centre has now started recruiting, and a third is expected to follow. Recruitment is expected to be finished by the end of 2027.

## Discussion

In this article, we describe the rationale and design of the SMILe (Spinal Morphine or Intravenous Lidocaine) study, a randomised assessor-blinded multicentre trial, investigating whether morphine spinal is superior to intravenous lidocaine in patients undergoing robot-assisted upper urinary tract surgery under general anaesthesia. Outcome measures include primarily PROM but also measures related to logistics, haemodynamics and inflammation.

At present, these procedures are associated with significant postoperative pain, and additional measures to improve postoperative recovery are thus warranted. Morphine spinal is effective^43^; however, it has disadvantages limiting its use. Other possible methods have side effects related to renal function and/or tumour biology. Lidocaine infusion is a potential tool lacking these side effects; however, its use has been limited in Sweden, probably because of the fear of side effects usually associated with systemic administration of local anaesthetics.

This study will thus provide important information on the use of morphine spinal in robot-assisted procedures, which are expected to increase in frequency. The findings will either confirm the beneficial effects of morphine spinal in these and similar procedures or make it possible to, in good conscience, omit the technique. The study will also provide additional safety data on perioperative lidocaine infusion, which, given its potential favourable role on tumour biology,^44^ might lead to an increasing use of this modality also in other cancer-related surgical procedures.

MCID is defined as the smallest change in a treatment outcome that an individual patient would identify as clinically important and which would justify a change in the patient’s management. Originally, the MCID for the QoR-15 was reported to be 8,^35^ but in a more recent article, the MCID was updated to 6.^36^ Considering the invasive nature of spinal morphine and its related side effects such as hypotension, increased use of resources and the need for increased postoperative monitoring, we chose the more conservative MCID value of 8.

Allowing different types of anaesthetic management can be considered a limitation, as this may introduce confounding effects. After discussion within the trial group, we decided to recommend intravenous anaesthesia; however, inhalational anaesthesia was permitted when preferred because of factors such as TCI(target controlled infusion)-related side effects or local clinical routines. We believe that permitting different anaesthetic regimens enhances external validity, enabling the results to be applied to a broader clinical context.

Strengths of the study include its multicentre design which increases external validity. Also, recovery is measured in multiple ways at multiple time points, as are effects on haemodynamic and inflammatory parameters. The use of an active comparator is a strength since it increases the clinical benefit of key results. The use of a control group (primary or secondary) without additional intervention has been contemplated but rejected for the following reasons:

The relevant question is not primarily whether morphine spinal is effective in this setting but whether it is more effective than alternative methods with fewer disadvantages.It is deemed not feasible to perform spinal analgesia blinded. This would require either the administration of morphine spinal after induction of general anaesthesia, which is not a preferred method since it might increase the risk of neurological injury related to the spinal punction, or it would require the omittance of bupivacaine which we feel is an important component of the morphine spinal concept. Therefore, the risk of confounding by placebo expectations is decreased when using an active comparator.It is ethically questionable to assign study patients to a treatment arm which we know is associated with severe postoperative pain.

In conclusion, the SMILe study will establish whether morphine spinal improves postoperative recovery compared with intraoperative lidocaine infusion in patients undergoing robot-assisted upper urinary tract surgery. Also, the effects of these two treatment modalities on haemodynamics and inflammation will be studied.
